### Additional analyses

To evaluate potential differences in systemic inflammatory response after randomisation, the area under the curve of APACHE-II and Marshall scores from randomization to day 7 will be calculated and compared between treatment groups. A predefined subgroup analysis will be done for the occurrence of the primary endpoint in patients with an APACHE-II < 13 or an APACHE-II ≥ 13. The precise relation between the primary endpoint and the time between start of symptoms and start of EN will be analyzed using a generalized linear model with logarithmic link function and Bernouilli distribution, with independent variables time (between start of symptoms and start of EN), time*time, APACHE-II score prior to randomization, hospital and co-morbidity (i.e. cardiovascular disease, pulmonary disease, chronic renal insufficiency or diabetes) [24].

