**Methods/Design:**

The PYTHON trial is a randomised controlled, parallel-group, superiority multicenter trial. Patients with predicted severe acute pancreatitis (Imrie-score ≥ 3 or APACHE-II score ≥ 8 or CRP > 150 mg/L) will be randomised to EN within 24 hours or an oral diet and EN if necessary, after 72 hours after hospital admission.

During a 3-year period, 208 patients will be enrolled from 20 hospitals of the Dutch Pancreatitis Study Group. The primary endpoint is a composite of mortality or infections (bacteraemia, infected pancreatic or peripancreatic necrosis, pneumonia) during hospital stay or within 6 months following randomisation. Secondary endpoints include other major morbidity (e.g. new onset organ failure, need for intervention), intolerance of enteral feeding and total costs from a societal perspective.

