### Secondary endpoints

Attenuation of the acute inflammatory response is hypothesized to be part of the beneficial effect of very early feeding on outcome thus secondary endpoints to assess such an effect are:

• Daily APACHE-II scores (see Additional file 1; Table S3), SIRS (presence, onset, duration, see Additional file 1; Table S4), CRP, and white cell count during the first week following randomisation.

• The individual components of the primary endpoint, need for and number of interventions (percutaneous or endoscopic transgastric drainage, surgical or endoscopic necrosectomy, other operations), use of antibiotics, length of hospital stay and in-hospital mortality.

• New onset organ failure (single or multi-system organ failure, timing and duration of failure), daily Marshall scores and need for and duration of ICU admission at any time during follow-up (for definitions see Additional File 1; Table S1 and Table S2).

Other secondary outcome measures are:

• The presence of peripancreatic and pancreatic necrosis on contrast enhanced computed tomography (CT) and the CT Severity Index (CTSI) as measured 5-7 days after admission. Peripancreatic necrosis (only) is defined as persistent peripancreatic fluid collections on a CT performed more than 14 days after admission in the absence of pancreatic parenchymal necrosis.

• Abdominal pain as daily measured by the Visual Analogue Scale (VAS).

• Proportion of daily nutritional target achieved at 1 week after admission.

• Nutrition related complications: diarrhea, aspiration pneumonia, need for conversion from EN to PN or additional PN and need for replacement of nasojejunal feeding tube after dislocation.

• Number of days until intake of solid food.

• Number of patients without the need for tube feeding in the selective delayed EN Group.

• Proportion of cross-over between both study arms.

• Hand grip muscular strength measured by the Jamar dynamometer.

• Quality of life measured by the EQ5D and SF-36 questionnaires.

• Total direct medical and indirect costs from a societal perspective during admission and until 6 months after discharge (details are available in the Additional File 1).

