### Study Population

All patients admitted with a first episode of acute pancreatitis to one of the 20 participating hospitals of the Dutch Pancreatitis Study Group (DPSG, hospitals are listed below) will be assessed for eligibility within 24 hours after hospital admission. Potential eligible patients are followed during the first 24 hours after admission until eligibility is established or the first 24 hours following admission have passed. If patients are classified as 'predicted severe' acute pancreatitis, they are included and stratified for hospital and APACHE-II score <13 or ≥13 and randomised in a 1:1 ratio, to receive early EN or an oral diet or EN if necessary at 72 hours after admission (figure 1) [20].

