### Group B: oral diet and EN if necessary at 72 hours after admission

Following randomisation, patients will be kept 'nil by mouth' without any artificial nutrition during the first 72 hours after admission (figure 2). If patients spontaneously request for oral food within these 72 hours, liquid and solid food are offered as requested and tolerated ("*ad libitum*"). If, at 72 hours after admission, patients develop organ failure, they will receive nasojejunal feeding with the same regimen as in group A. If, at 72 hours, there is no organ failure, patients are offered oral food *ad libitum*. If oral food is not tolerated, there is a re-challenge the next morning and if still not tolerated, EN is started through a nasojejunal feeding tube.

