## Statistical Aspects

### Sample size calculation

The PYTHON trial is a superiority trial, hypothesizing a reduction in the primary endpoint in favour of early EN as compared to the current practice of an oral diet and EN, if necessary at 72 hours after admission. Data from patients in the PROPATRIA trial are used to calculate sample size [23]. All patients in the placebo-arm of the PROPATRIA trial received EN via a nasojejunal feeding tube. Patients from the PROPATRIA trial that fulfilled the PYTHON inclusion criteria (predicted severe acute pancreatitis < 24 hours after admission) were evaluated. In these patients EN was initiated after a median of 3 days. This equals the standard group in the PYTHON trial. In 39% of these patients an infection (bacteraemia, pneumonia, infected necrosis) occurred. The mortality in the placebo arm of PROPATRIA was 6%. All studies included in a meta-analysis performed by our group on EN versus PN that initiated EN within 24 hours after admission were selected [17]. In these patients (receiving EN within 24 hours), infections were diagnosed in 22% and mortality was 5%. Therefore, the expected reduction in mortality is only 1%. When mortality and infections are combined in the primary composite endpoint, an absolute reduction of 18% is expected (from 40 to 22%). With 80% power, two-sided 5% alpha and 1% loss to follow-up the sample size was set at 208 patients [http://www.stat.ubc.ca/~rollin/stats/ssize/b2.html].

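### The planned model of outcome on time to start of EN is open to selection bias and overloaded: controls who eat have no EN start time, and controls who get EN are mostly selected by later severity or intolerance

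*Protocol article*

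**What the plan says.** The Additional analyses section of the protocol article announces: "The precise relation between the primary endpoint and the time between start of symptoms and start of EN will be analyzed". The model is a generalised linear model with log link and Bernoulli distribution. Besides time it contains "time*time, APACHE-II score prior to randomization, hospital and co-morbidity", where co-morbidity covers four conditions.

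The Group B section sets out when a control patient receives EN. Organ failure at 72 hours leads to tube feeding. Without organ failure the patient is offered oral food, and then: "If oral food is not tolerated, there is a re-challenge the next morning and if still not tolerated, EN is started". A patient who eats therefore never starts EN. The protocol expects such patients, because the Secondary endpoints section counts them: "Number of patients without the need for tube feeding in the selective delayed EN Group".

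Three other sections bear on the model:
- The ICU section leaves route and type of feeding to the intensivist at any time, so an ICU patient may start EN early or receive parenteral nutrition only.
- The Exclusion criteria allow up to 96 hours of symptoms before admission.
- The Analyses section applies intention to treat, with all randomised patients, to every analysis.

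**The concern.** The exposure is fixed by the protocol, but it does not exist for a group that the protocol itself anticipates. Those patients cannot enter the model as written, so the all-randomised rule cannot be met.

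The controls who remain are not a random subset. Most start EN because they developed organ failure or could not tolerate food, and both arise after randomisation. The severity covariate is measured before it. The endpoint counts from randomisation, so an infection can also precede the EN start that is meant to explain it.

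Late EN would then partly mark a worse course. A finding that later feeding goes with more infections could arise without any effect of timing, and it would be read as support for the trial's hypothesis. Separately, 20 hospitals in a log-link model leave few events for each parameter.

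**Working it through.** **Inputs.** Control and early-EN risks of 40% and 22% (Sample size calculation). Allocation: "randomised in a 1:1 ratio". Hospitals: "208 patients will be enrolled from 20 hospitals of the Dutch Pancreatitis Study Group". The plan's own figure: "With 80% power, two-sided 5% alpha and 1% loss to follow-up the sample size was set at 208 patients".

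**Reproducing 208.** Pooled-variance formula without continuity correction, mean risk (0.40 + 0.22)/2 = 0.31:

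n = [1.96·√(2·0.31·0.69) + 0.842·√(0.40·0.60 + 0.22·0.78)]² / 0.18² ≈ 102.5, so 103 per arm and 206 in total. Allowing for 1% loss, 206/0.99 = 208.1. The stated figure reproduces.

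**Events and parameters.**
- Events: 104 × 0.40 + 104 × 0.22 = 41.6 + 22.9 = 64.5, about 3 per hospital.
- Parameters: intercept 1 + time 1 + time squared 1 + APACHE-II 1 + hospital 19 + co-morbidity 4 = 27, or 24 if co-morbidity is one yes/no term.
- Events per parameter: 64.5/27 = 2.4, or 64.5/24 = 2.7. Without hospital indicators: 64.5/8 = 8.1.

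These are upper limits. If a share q of controls never starts EN and has risk r₀, the events left are 104 × 0.22 + 104 × (0.40 − q·r₀). For assumed q of 20 to 70% and r₀ of 10 to 40% (leaving out combinations that would need a risk above 1 in the other controls), about 35 to 62 events in 135 to 187 patients remain. That is 1.3 to 2.6 per parameter.

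**Selection with no true timing effect.** Assume 31% risk in both arms. The documents give neither the share of controls needing EN nor their risk, so both are varied.
- If a share s of controls needs EN with k times the risk of those who eat, the crude late-versus-early risk ratio is k/(1 + s(k − 1)). For s = 0.7, k = 1.5: 1.5/1.35 = 1.11. For s = 0.3, k = 2: 2/1.3 = 1.54. Between 0.3 × 104 = 31 and 0.7 × 104 = 73 controls have no exposure value.
- If 30 to 50% of controls never need EN and have 10 to 20% risk, the ratio is (0.31 − q·r₀)/((1 − q)·0.31). For q = 0.3, r₀ = 0.20 it is 0.357/0.31 = 1.15; for q = 0.5, r₀ = 0.10 it is 0.52/0.31 = 1.68.

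**Illustrative simulation under the null, with adjustment.** A latent severity drives both the need for EN and the outcome, and baseline APACHE-II captures it only in part. The test came from a robust Poisson model with linear time, APACHE-II and four co-morbidities, without hospital or time squared, so it is simpler than the planned model. There were 300 runs per setting.

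| Controls never on EN (assumed) | Time significant at 5% | Median risk ratio per 3 days |
|---|---|---|
| about 0% | 5% | 1.02 |
| 30% | 11% | 1.13 |
| 50% | 27% | 1.28 |

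The simulation error is about √(0.27 × 0.73/300) = 2.6 percentage points at most. In this set-up the rate rises further with larger shares. Another set of assumptions gave 11 to 22%, with risk ratios of 1.05 to 1.15 per 48 hours.

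**Fitting.** With 19 hospital indicators, a standard log-binomial routine gave no usable fit in over 90% of simulated data sets.

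**The case against.** *The direction is not fixed.* A reader might infer that the model would show harm from late feeding and so favour the hypothesis. The documents do not support that certainty. ICU patients may be fed at any time, so some of the sickest controls may start EN early, which pushes the other way. The exposure also includes up to 96 hours of pre-admission delay that was not randomised. The crude ratios of 1.11 to 1.68 ignore the planned adjustment, and after adjustment most null runs were not significant. What stands is an inflated error rate with a likely, not a certain, direction.

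*Convergence depends on the routine.* A reader might infer that the model cannot be fitted. In 100 simulated data sets where default fitting gave a valid result in 8%, a constrained maximum-likelihood optimiser converged in all. The protocol names no routine. Estimates for hospitals with about three expected events would still be unstable or lie on a boundary.

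*Some of this belongs in an SAP.* Coding of hospital and co-morbidity, a fallback for non-convergence and a rule for patients without EN are commonly left to it. That is fair, and the parameter count is therefore conditional on 19 indicators. Such details would not remove the selection, because outcome, exposure and severity covariate are already fixed in the protocol article.

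*It is a secondary matter.* The section is headed Additional analyses and speaks of a relation, not a causal effect. This limits the consequence, but the wording still promises precision that the design cannot give.

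**Conclusion.** The concern holds in a bounded form. The exposure is undefined for controls who never start EN, which conflicts with including all randomised patients. Among the controls who remain, EN mostly follows post-randomisation organ failure or intolerance, which baseline APACHE-II does not capture. The nominal 5% test of time rose to about 11 to 27% in the illustrative simulations. These rest on assumed shares and risks and on a simplified model, so they show the order of the problem and do not predict the result. If hospital is entered as 19 indicators, 2.4 to 2.7 events per parameter at best make instability or failure with standard routines likely.

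A reader might go further and infer that the trial's main conclusion is at risk. It is not: the intention-to-treat comparison of the primary endpoint and the sample size do not use this model. The point should be corrected, but it does not threaten the trial.

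**What to change.** Make the pre-specified timing analysis an intention-to-treat model on all randomised patients: Poisson regression with robust variance, with arm, time from symptom onset to randomisation, arm-by-time and APACHE-II stratum (below 13, or 13 and above). Handle hospital as a random intercept or as the cluster, not as 19 indicators. With the intercept this has 5 fixed parameters, or 64.5/5 = 12.9 expected events each.

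If the model on achieved time to EN is kept, label it exploratory and non-causal, report by arm how many patients have no EN start, and drop the claim of a precise relation.

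The cost is a change of wording. Time from symptom onset to randomisation is already listed as a baseline characteristic, so no new data are needed. With 142 of 208 patients randomised when the article was written, the change could still precede the analysis. The replacement addresses timing at baseline and not achieved feeding time, and its interaction test will have low power at about 64 events.

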### Premature termination of the study

An interim-analysis is performed on the primary endpoint when 50% of patients have been randomised and have completed the 6 months follow-up. The interim-analysis is performed by an independent statistician, blinded for the treatment allocation. The statistician will report to the independent DSMC. The DSMC will have unblinded access to all data and will discuss the results of the interim-analysis with the steering committee in a joint meeting. The steering committee decides on the continuation of the trial and will report to the central ethics committee. The Peto approach is used: the trial will be ended using symmetric stopping boundaries at P < 0.001 [25]. The trial will not be stopped in case of futility, unless the DSMC during the course of safety monitoring advices otherwise. In this case DSMC will discuss potential stopping for futility with the trial steering committee.

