### Data collection and follow-up

Follow-up visits will take place at 3 and 6 months after discharge. Data collection will be performed by local physicians using a written case-record form. An independent auditor will check all primary and secondary endpoints and at least 10% of data in case-record forms against on-site source data. Discrepancies detected by the auditor will be resolved on the basis of consensus by two investigators unaware of the study-group assignment and not involved in patient care.

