### Analyses

All analyses will be according to the intention-to-treat approach in which all randomised patients are included, regardless of adherence to study protocol. After the last patient in the trial has completed follow-up, an adjudication committee blinded for treatment allocation will evaluate each patient using the raw data for the possible occurrence of the primary endpoint. Disagreements will be resolved in a plenary consensus meeting. Occurrences of the primary and secondary endpoints are compared between the treatment groups. Results are presented as risk ratios with corresponding 95% confidence intervals. A two-tailed P < 0.05 is considered statistically significant.

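### The interim stopping rule is applied to the primary endpoint before the blinded committee has adjudicated any patient; the risk is modest and the remedy cheap

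*Protocol article*

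**What the plan says.** Four statements in the protocol article bear on this.

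- **Interim (Premature termination of the study, under Statistical Aspects).** "An interim-analysis is performed on the primary endpoint when 50% of patients have been randomised and have completed the 6 months follow-up". Its stopping rule is that "the trial will be ended using symmetric stopping boundaries at P < 0.001". On blinding, "The interim-analysis is performed by an independent statistician, blinded for the treatment allocation". The DSMC sees all data unblinded and meets the steering committee, after which "The steering committee decides on the continuation of the trial and will report to the central ethics committee".
- **Adjudication (Analyses).** "After the last patient in the trial has completed follow-up, an adjudication committee blinded for treatment allocation will evaluate each patient", working from the raw data, with disagreements settled in a plenary meeting.
- **Data source (Data collection and follow-up).** "Data collection will be performed by local physicians using a written case-record form".
- **Audit (same section).** "An independent auditor will check all primary and secondary endpoints and at least 10% of data in case-record forms against on-site source data". Then: "Discrepancies detected by the auditor will be resolved on the basis of consensus by two investigators unaware of the study-group assignment". No timing is given for either step.

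The Rationale for design section explains that a double-blind design was not possible, because one arm receives a feeding tube from the start and the other is offered an oral diet first.

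**The concern.** The plan treats blinded review of every patient as necessary for the final primary result, yet the one analysis that can end the trial early comes before that review. The interim statistician's blinding protects the calculation, not the way events were classified. The events themselves are recorded at the hospitals, where staff will normally know whether a patient was tube-fed from the start.

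Two errors are possible. Differential recording could push the comparison over the boundary; the trial would stop, and the adjudication that follows might not support the result that stopped it. The article has no rule for that case. Alternatively, random misclassification could dilute a real difference, so that a true crossing is missed. The second error matters less, because the trial would then run to its planned size and be analysed on adjudicated events.

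**Working it through.** **1. Order of events.** The sample size section gives 208 patients, so 50% is 104, about 52 per arm at 1:1 allocation. The article plans accrual over three years. Assuming uniform accrual:

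- 104th patient at month 18; plus 6 months of follow-up gives interim data at about month 24.
- 208th patient at month 36; plus 6 months means adjudication can start at about month 42.
- Gap: 42 − 24 = about 18 months.

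No section mentions an adjudication round inside that gap.

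**2. The plan's own figure.** Inputs from the sample size section: 40% vs 22%, 80% power, two-sided 5%, 1% loss. With the pooled-variance formula without continuity correction and mean rate 0.31:

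n = [1.960·√(2·0.31·0.69) + 0.842·√(0.40·0.60 + 0.22·0.78)]² / 0.18² = 102.4, so 103 per arm, 206 in total. Then 206/0.99 = 208.1, which agrees with the stated 208.

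**3. Where the boundary lies.** The article does not name the interim test. For a pooled two-proportion z-test with 52 per arm, z = (c − e)/52 ÷ √(p(1 − p)·2/52), where c and e are the control and early-EN event counts and p = (c + e)/104. Take 21 control events (40.4%):

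| Early-EN events | z | P, pooled z | P, Fisher exact |
|---|---|---|---|
| 5 | 3.62 | 0.0003 | 0.0005 |
| 6 | 3.35 | 0.0008 | 0.0014 |
| 7 | 3.09 | 0.0020 | 0.0036 |

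The last count that stops the trial is 6 under the z-test and 5 under Fisher's test.

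**4. False crossing in favour of early EN when there is no true effect.** Exact binomial, pooled z, two-sided P < 0.001, 52 per arm. Recording is assumed to move the control rate up by d/2 and the early-EN rate down by d/2. The values of d are assumptions; the article gives none.

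| d | Common rate 31% | Common rate 40% |
|---|---|---|
| 0 | 0.05% | 0.05% |
| 5 points | 0.28% | 0.27% |
| 10 points | 1.3% | 1.2% |

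**5. Missed crossing at the design effect.** With correct classification at 40% vs 22%, the chance of crossing is 9.0%. Non-differential error changes each rate to p·sens + (1 − p)(1 − spec), again with assumed values:

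- Sensitivity 0.90, specificity 0.95: observed rates 39.0% vs 23.7%, crossing 5.0%.
- Sensitivity 0.80, specificity 0.90: observed rates 38.0% vs 25.4%, crossing 2.6%.

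**The case against.** There is a good case that this matters little.

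- **The audit is more than a check of entries.** Every endpoint is compared with source data, and discrepancies go to two investigators who do not know the allocation and are not involved in care. Nothing defers this to the end of the trial. This stands, so it would be wrong to infer that the interim rests on raw local reports with no blinded input. But the step reaches only what the auditor flags, its timing is open, and it is not the patient-by-patient evaluation that the Analyses section requires.
- **Most components follow written criteria.** Table 1 of the article defines infected necrosis by culture or by gas on CT, and bacteraemia by blood culture with a two-sample rule for non-pathogens. Death is objective. This stands: pneumonia leaves the most room for judgement. Knowledge of the arm could also affect when cultures are taken, but adjudicating existing records would not repair that.
- **The one-patient margin proves little.** A reader might infer from the table of P values that the decision is unusually fragile. Any threshold behaves this way at its edge, adjudicated or not, and the exact cut-off depends on a test that the article does not name.
- **The article is condensed.** The adjudication sentence could be read as describing only the final analysis, with the interim's data version left to a fuller document. That is possible. Still, the article positively places the committee's work after the last follow-up, so an earlier round specified elsewhere would conflict with this text. That makes it more than an omitted detail.

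**Conclusion.** The point holds as a matter of sequence: as written, the stopping rule acts on events that the blinded committee has not yet seen. It is an improvement worth making, not a flaw that undermines the trial. Under the assumed 5- and 10-point reporting shifts, a false stop favouring early EN has a probability of about 0.3% or 1.3%, against about 0.05% without a shift. Even at the design effect the boundary is crossed only 9.0% of the time. If the trial continues, the final analysis uses adjudicated endpoints and is unaffected.

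A reader might infer that an early stop would probably be spurious, or that the final result is compromised. The documents support neither: they give no misclassification rates, the boundary is strict, and the DSMC and steering committee review the data before any stop. What remains is that a stop cannot be undone, later adjudication could contradict it, and the article does not say what would follow. The sizes rest on 52 per arm, a pooled z-test and assumed error rates.

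**What to change.** Amend the Analyses and Premature termination sections together so that:

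1. the blinded committee adjudicates the first 104 patients before the interim data are frozen;
2. the interim analysis uses only those adjudicated events;
3. those decisions carry forward unchanged to the final analysis.

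The cost is one earlier committee round and possibly a few weeks' delay to the interim. Total adjudication work, the sample size of 208 and the P < 0.001 boundary do not change.

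A lighter alternative is to state that the interim uses audited, unadjudicated events and that any crossing must be confirmed by blinded adjudication before the steering committee decides. That guards against a stop which adjudication would contradict, but not against a missed crossing. Neither option removes bias from differential decisions to take cultures.

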### Randomisation

Randomisation is performed centrally by the study coordinator using an internet randomisation module (Julius Center for primary care and health sciences, University Medical Center Utrecht, the Netherlands). Randomisation is stratified according to the predicted severity of disease ('predicted moderate severe' vs. 'predicted very severe'; APACHE-II < 13 or ≥ 13) and according to hospital. Permuted-block randomisation with varying block size is used and block size is concealed to all local investigators.

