### Safety

An independent data and safety monitoring committee (DSMC) will evaluate the progress of the trial and will examine safety variables after every 25 patients have completed the 6 months follow-up. This evaluation is based on unblinded data, in the presence of the study coordinator as far as the 'explanatory part' of the meeting is concerned. After full explanation of the data presented, the study coordinator is dismissed and the DSMC discusses the consequences of the data presented. Adverse events are defined as 'any undesirable experience occurring to a subject during a clinical trial, whether or not considered related to the intervention' (i.e. early enteral nutrition). All involved physicians will repetitively be asked to report any potential adverse events. These adverse events will be listed and discussed with the DSMC. The outcome of the meeting of the DSMC will be discussed with the trial steering committee. The outcome will also be sent to the Utrecht institutional review board (IRB). The data of the deceased patients will be evaluated by the DSMC for cause of death and possible trial related serious adverse events. All possible adverse events will be reported to the Central Committee on Research involving Human Subjects (Centrale Commissie Mensgebonden Onderzoek [CCMO]) and the IRB using the online module https://toetsingonline.ccmo.nl 

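### Open-label trial: the coordinator is present while unblinded data are explained, and interim results are discussed with the steering committee even if the trial continues

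*Protocol article*

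**What the plan says.** The protocol article sets out two separate flows of information.

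- **Safety reviews (Safety).** The DSMC "will examine safety variables after every 25 patients have completed the 6 months follow-up". Of these reviews the article says: "This evaluation is based on unblinded data, in the presence of the study coordinator as far as the 'explanatory part' of the meeting is concerned". The coordinator leaves before the deliberation, but only once the data have been presented: "After full explanation of the data presented, the study coordinator is dismissed". The outcome of the meeting is then taken to the steering committee.
- **Interim analysis (Premature termination of the study).** At 50% of patients with completed follow-up, an independent statistician who is blinded to allocation analyses the primary endpoint and reports to the DSMC. The DSMC has unblinded access to all data and "will discuss the results of the interim-analysis with the steering committee in a joint meeting". Then: "The steering committee decides on the continuation of the trial".

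Under Randomisation: "Randomisation is performed centrally by the study coordinator using an internet randomisation module". The same section states that "block size is concealed to all local investigators"; it does not mention the coordinator in this respect.

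Under Rationale for design, the article explains that patients cannot be blinded. Under Analyses, a blinded committee adjudicates the primary endpoint after the last patient has completed follow-up.

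**The concern.** The usual separation is that people who run a trial see pooled data, and only the monitoring committee sees data by arm. Here the coordinator is kept out of the discussion but not away from the data. The steering committee discusses the interim results themselves rather than receiving a recommendation.

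This matters more than usual in this trial for two reasons. First, care is open-label, so anyone who knows the trend also knows which arm a given patient is in. Second, by the definitions in Table 1 most infection components need a test that somebody orders: a blood, sputum or endotracheal culture, a chest radiograph, an aspirate or a CT. Trial leaders who know the running difference could, without intending to, affect recruitment, how hard infection is looked for, or the decision to continue. Adjudication at the end classifies what was recorded. It cannot supply a culture that was never taken.

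**Working it through.** **1. The plan's own figure.** Inputs from Sample size calculation: 40% versus 22%, two-sided 5% alpha, 80% power, 1% loss. The mean rate is (0.40 + 0.22)/2 = 0.31. With pooled variance under the null and no continuity correction:

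n per arm = [1.960·√(2·0.31·0.69) + 0.842·√(0.40·0.60 + 0.22·0.78)]² / 0.18² = 102.4, so 103 per arm and 206 in total.

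206/0.99 = 208.1, which agrees with the stated 208.

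**2. Would the trial normally stop at the interim?** Half of 208 is 104, or 52 per arm. Two-sided P < 0.001 needs z = 3.29.

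- Standard error under the null: √(2·0.31·0.69/52) = 0.0907.
- Difference needed: 3.29 × 0.0907 = 0.298, about 30 percentage points.
- Standard error under 40% versus 22%: √[(0.40·0.60 + 0.22·0.78)/52] = 0.0890.
- Power to cross: Φ[(0.18 − 0.298)/0.0890] = Φ(−1.33), about 9%.

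Even if the design hypothesis is exactly right, about nine times in ten the trial goes on after the steering committee has discussed the result.

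**3. Is formal alpha affected?** With 0.001 at half information and 0.05 at the end (correlation √0.5), overall two-sided alpha is about 0.0502. The issue is operational bias, not the stopping rule.

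**4. How much of the trial could be exposed?** Assumption: even accrual of 208 patients over the planned 3 years, 208/36 = 5.78 per month, with each look 6 months after the last patient it needs.

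- First review: 25/5.78 + 6 = 10.3 months. About 60 patients are already enrolled, leaving 148/208 = 71% to come.
- Interim: 104/5.78 + 6 = 24 months. About 139 are already enrolled, leaving 69/208 = 33% to come.
- 208/25 gives 8 reviews. The sixth falls at 32.0 months and the seventh at 36.3 months, so about 6 fall during recruitment.

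**5. Illustration of size.** Assumptions, none of them in the documents: no true effect, a 31% event rate, 103 per arm, and a relative share of 10% or 20% of events missed in one arm among exposed patients only. The observed rate in that arm is 0.31 × (1 − exposed share × missed share). The figures are rejection probabilities of the two-sided 5% two-proportion test.

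| Exposed patients | 10% missed | 20% missed |
|---|---|---|
| Enrolled after the first review (71%) | rate 28.8%, about 6.4% | rate 26.6%, about 10.7% |
| Enrolled after the interim (33%) | rate 30.0%, about 5.3% | rate 29.0%, about 6.2% |

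These count later enrolments only. Some patients already enrolled at a look could still have later events, which would raise the figures. Faster accrual would lower them, because more patients would be in before each look; Recruiting success reports inclusion ahead of schedule.

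**The case against.** Several objections carry weight.

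- **The two flows are different.** The coordinator's presence is described for reviews of safety variables, not expressly for the primary-endpoint interim. The article does not say that the steering committee sees results labelled by arm. That is an inference, though a fair one: an unblinded DSMC discusses the results with the committee and no restriction is stated.
- **Tampering with allocation.** A reader might infer this from the coordinator's double role. The article does not support it. Allocation runs through a central internet module with stratified permuted blocks of varying size, and no route from safety data to allocation is shown.
- **The steering committee decides.** A reader might take this as a fault in itself. It is not: a DSMC commonly advises and a steering committee decides. The issue is what the committee is told first.
- **Size.** A reader might apply under-detection to all 103 patients in one arm and obtain about 7.8% or 16.8%. The plan's timing rules that out, because every look waits for 6 months of completed follow-up.
- **The causal chain is partly general.** Treating physicians in 20 hospitals order the tests, and nothing says that interim results reach them. Differential testing can occur in any open-label trial, and the fix would not remove that part.
- **Safeguards exist.** These are blinded adjudication from raw data, an independent audit of all endpoints with discrepancies resolved by blinded investigators, a fixed boundary, and no routine stopping for futility. The blinded statistician protects only the calculation. The others limit misclassification and discretion, but do not act on recruitment or on tests not done.

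One could add that session structure is usually left to a charter. That would answer a gap. Here the article positively prescribes who is present and what is discussed, so silence is not the problem.

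**Conclusion.** The concern stands in this limited form. In an open-label trial, the article prescribes that the coordinator who performs randomisation is present while unblinded data are explained, and that interim results are discussed with the steering committee whether or not the boundary is crossed. With about 9% power to cross under 40% versus 22%, continuation with leadership aware of the trend is the likely course. The risk concerns recruitment, infection work-up and the continuation decision.

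The size cannot be derived from the documents. Under the stated assumptions, type I error would be between about 5.3% and 10.7% instead of 5%. The low end assumes 10% missed after the interim only; the high end assumes 20% missed after the first review. The documents do not show that any such under-detection occurs, and the formal error rate is essentially intact.

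**What to change.** - **Safety.** Split each DSMC meeting. The coordinator attends only an open session with pooled data. By-arm data are shown in a closed session of the DSMC and the independent statistician.
- **Premature termination of the study.** Replace discussion of the interim results with a recommendation to the steering committee: continue, modify or stop. Release by-arm results only if the DSMC recommends stopping. The steering committee keeps the decision.
- **Record.** Document who has already seen by-arm data, and when. The article reports 142 patients randomised, so later looks can still be protected, but past disclosure cannot be undone.

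Cost: a change of wording in the protocol and DSMC charter. No patients are added, and the DSMC and independent statistician already exist. The small downside is that the steering committee acts on a recommendation instead of the figures.
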